6.1 Screening and enrolment

All patients who meet the basic enrolment criteria (age, fever or history of fever, symptoms of malaria, absence of signs of severe malaria, absence of severe malnutrition, pregnancy) during screening will be assigned a consecutive number and evaluated in greater depth by clinical staff. The screening record form (Appendix 5) will be used to record the general information and the clinical observations on each patient being screened. If the patient meets the clinical criteria, he or she will be examined for parasitaemia. Once the patient meets all the enrolment criteria, he or she will be asked for consent to participate in the study.

6.2 Follow-up

Patients who meet all the enrolment criteria will be given a personal identification number and will receive treatment only after the study has been fully explained to them and they have willingly provided informed consent. Any person who decides not to participate in the study will be examined, treated and followed-up by the health facility staff according to the standard of care established by the Ministry of Health.

The basic follow-up schedule is summarized in Appendix 6. A case report form (Appendix 7) and a serious adverse event report form (Appendix 8) will be used to record the general information and clinical observations on each patient enrolled into the study. The appointment schedule will be clearly explained, and a follow-up card with a personal identification number will be provided.

The day a patient is enrolled and receives the first dose of medicine is designated ‘day 0’. All antimalarial treatment will be given by a study team member under supervision. Enrolled patients will be observed for at least 30 min after treatment to ensure that they do not vomit the medicine. If vomiting occurs within 30 min of treatment, the full treatment dose will be repeated. Ancillary treatment, such as antipyretics, will be provided if necessary to patients by the study team and documented on the case report form. Patients with persistent vomiting (i.e. necessitating more than a single repeat dose) will be excluded from the study and immediately referred to the health facility staff for appropriate management.

Thereafter, patients are required to undergo regular clinical reassessment. Blood films for parasite counts will be made twice a day (12 hourly) til parasite clearance and then on day 7 and then weekly for the remainder of the follow-up period, i.e. on days 14, 21, and 28. Patients will be advised to return on any day during the follow-up period if symptoms return and not to wait for the next scheduled visit day. Clinical reassessment will be sufficiently thorough to ensure patient safety and will include assessment not only for potential treatment failure but also for potential adverse reactions to the medicine. Additionally, blood films will be obtained whenever parasitological reassessment is requested by the clinical staff.

Because many medicines have to be given over several days, the initial visits are critical not only for assessing efficacy but also for ensuring patient safety; defaulters at this stage will not have received a complete course of treatment and may be at risk for clinical deterioration. All reasonable efforts will be made to find defaulters to ensure complete treatment. Similarly, the ultimate success of the study rests on minimizing loss to follow-up. While patients are encouraged to return on their own for scheduled follow-up visits, it is essential that provisions be made ahead of time for locating patients at home if they do not attend as requested. This requires obtaining detailed directions to the home during enrolment, and study team members familiar with the community will be responsible for home visits and means of transport for the patients. The schedule of treatment and follow-up examinations given in this protocol must be followed to ensure data integrity. After day 7 patients who fail to return on day 14 but are present on day 13 or 15 (likewise days 20/22, days 27/29) may still be included in the analysis. Deviation from the protocol of more than 1 day should, however, be avoided (see also section 3.7).

7. Data management

The principal investigator will ensure that the study protocol is strictly adhered to and that all data are collected and recorded correctly on the case report form. Laboratory and clinical data will be recorded on a daily basis on the case report form designed for the study. Data derived from source documents should be consistent with the source documents, or the discrepancies should be explained. Any change or correction to a case report form should be dated and explained and should not obscure the original entry. All case report forms will be checked for completeness.

After the study has been completed, data will be entered into a database by double independent data entry, according to WHO standard procedures.[[3]](#footnote-4) The trial data will be stored in a computer database, maintaining confidentiality.

The principal investigator is responsible for keeping all screening forms, the case report form and the completed subject identification code list in a secure location.

8. Statistical methods

8.1 Sample size

The estimated prevalence of patients positive at day 3 after artesunate 4 mg/kg/day over 7 day in the area is 15%. At a confidence level of 95% and a precision around the estimate of 10%, a minimum of 40 must be included. With a 20% increase to allow loss to follow-up and withdrawals during the 28-day follow-up period, a number of 50 patients should be targetted in the study per site.

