Recently, longer parasite clearance and decreasing efficacy of ACTs were observed in Shwe Kyin and Kawthaung, on the south eastern tip of Myanmar bordering with Ranong, Thailand. A total of 168 cases were completed for study in artemether-lumefantrine group and 153 in dihydroartemisinin-piperaquine group. There was one ETF case at Shwe Kyin, who had persistence of parasitemia up to day 3 with parasite count more than 10% of the day 0 count. Clinically 8 recurrence cases in artemether-lumefantrine group and 4 cases in dihydroartemisinin-piperaquine group were noted, but reinfection can be excluded after molecular analysis. The persistant of parasitaemia was noted in all study sites for both combinations and marked elevation was noted in patients treated with dihydroartemisinin-piperaquine at Kawthaung (18.5%). This same site in Thailand has been showing increasing artesunate-mefloquine failures since 2006. The presented results of that therapeutic efficacy trials in Cambodia and Thailand were the failure rates of combinations with artemisinin derivatives and mefloquine and artemether-lumefantrine in both countries, as well as increased parasite clearance time (PCT) from clinical trials using artesuante-mefloquine and artesunate+pyronaridine in Cambodia. Of the data presented from the two countries, the slow PCT following treatment with artemisinin derivatives was of greatest concern. With combination therapy, artesunate usually provides the initial rapid decrease of PCT, with 95% of patients clearing peripheral parasitaemia within 48 hours, hence if the PCT is slow despite the drug being in the blood at adequate levels, this could provide evidence that it is failing. The resistance monitoring shows the proportion of patients who are parasitaemic on day 3 is the best measure of slow parasite clearance from available clinical trial data and should be used as an early warning system for development of artemisinin resistance.

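### Section 8.1's minimum of 40 patients does not give 10-point precision at 95% confidence for a 15% day-3 positivity rate; its own inputs require 49

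*Protocol*

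**What the plan says.** Section 8.1 gives three inputs and a result. The expected day-3 positivity after the study regimen is 15%. The confidence level and precision follow, with the number drawn from them: "At a confidence level of 95% and a precision around the estimate of 10%, a minimum of 40 must be included". The section then adds an allowance: "With a 20% increase to allow loss to follow-up and withdrawals during the 28-day follow-up period, a number of 50 patients should be targetted". It gives no formula, names no interval method and applies no finite-population correction.

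Other parts of the protocol bear on the point:

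- Section 5 lists the number of patients positive at day 3 among the end-points, and section 1 treats that proportion as an early signal of emerging artemisinin resistance.
- Section 5.1.1 describes the study as descriptive, so the sample size rests on precision alone.
- Sections 3.2 and 3.3 keep patients in hospital for the first 7 days.
- Section 8.2 attaches 95% confidence intervals to losses and withdrawals and to the day-28 outcome categories. For day-3 positivity it lists only the number of patients.

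**The concern.** Section 8.1 is the protocol's only quantitative justification of the trial size, and its result does not follow from its inputs. Because 50 is obtained from 40, the section also tells the study team that 40 evaluable patients are enough for the claimed precision.

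The section also mixes two time points. The quantity being sized is read on day 3, whereas the allowance is for losses over 28 days. A reader cannot tell whether 40 is meant as the number with a day-3 result or the number still under observation at day 28.

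What is at stake is the accuracy of a stated precision. The indicator concerned feeds into the judgement, set out in section 2, of whether artemisinin resistance is present and whether containment should begin.

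**Working it through.** **Inputs, all from section 8.1.** Expected proportion p = 0.15; confidence 95%; precision d = 0.10; stated minimum 40; allowance 20%; target 50. Two readings are assumed because the section does not spell them out: a two-sided interval (z = 1.96) and precision as an absolute half-width in percentage points.

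**The plan's own figures.**

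- The step from 40 to 50 reproduces: 40 / (1 − 0.20) = 50. A plain 20% increase would be 40 × 1.2 = 48.
- The minimum of 40 does not reproduce: n = z² p(1 − p) / d² = 3.8416 × 0.1275 / 0.01 = 48.98, rounded up to 49. That is 9 patients, or 22.5%, above 40.

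**Could another reading give 40?** The smallest n on the same 15% and 10%:

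| Reading | n |
|---|---|
| One-sided 95% (z = 1.645) | 35 |
| Arcsine | 48 |
| Two-sided Wald | 49 |
| Wilson half-width | 49 |
| z = 2 | 51 |
| Agresti-Coull | 52 |
| Clopper-Pearson half-width | 58 |
| Continuity-corrected | 59 |
| 10% as full width | 196 |
| 10% as relative precision | 2177 |

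None gives 40. It appears only if an unstated input is changed: a finite population of about 213 eligible patients, an expected rate of about 11.8%, or a precision of about 11 points.

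**What a given number of day-3 results delivers.** Half-width = 1.96 × √(0.1275 / n):

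| n with a day-3 result | Half-width (points) |
|---|---|
| 40 | 11.1 |
| 45 | 10.4 |
| 48 | 10.1 |
| 49 | 10.0 |
| 50 | 9.9 |

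**Confidence at which 40 gives 10 points.** The standard error at n = 40 is √(0.1275 / 40) = 0.0565. Then 0.10 / 0.0565 = 1.77, which corresponds to two-sided confidence of about 92.3%.

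**Carrying 49 through the same allowance.** 49 / 0.8 = 61.25, so 62; as a plain 20% increase, 49 × 1.2 = 58.8, so 59. These numbers apply only if a 20% loss is expected before the day-3 reading.

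**The case against.** The strongest reply is that the working number is the target of 50, not the minimum of 40. The endpoint is read on day 3, when patients are still in hospital, so few results should be missing, and 50 results give 9.9 points. Even at 40 the shortfall is only 1.1 points. The study is descriptive, with no test, margin or power claim that could be overturned. All of this stands and limits the consequence. It does not make 40 follow from the inputs.

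Three stronger readings are tempting, and the documents do not support them.

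- A reader might infer that the report will show an interval wider than promised. Section 8.2 does not commit to an interval for day-3 positivity, and with 50 results the claimed precision is met. A wider interval needs early losses.
- A reader might infer that the trial must recruit 59 to 62. The 20% allowance is for the 28-day period, so it cannot simply be applied to day 3. Equally, 40 cannot be taken as the expected number of day-3 results.
- A reader might rerun the calculation with the 18.5% persistence reported for Kawthaung in section 1. That figure is for dihydroartemisinin-piperaquine, its sentence does not name day 3, and section 8.1 makes its own 15% assumption for artesunate.

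On the other side, the margin at 50 is thin. Section 3.8 withdraws patients who vomit the medication twice or were wrongly enrolled, and section 5.2.4 excludes those whose species reading stays inconclusive. Two missing results take the half-width just past 10 points.

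**Conclusion.** The stated minimum is wrong on its own inputs: 49 is required, not 40, and 40 patients give about ±11.1 points at 95% confidence. The error is in the stated figure and carries into the derivation of 50, although 50 itself happens to satisfy the corrected minimum if at most one patient lacks a day-3 result.

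This rests on a two-sided 95% level, an absolute 10-point half-width, an observed rate close to 15% and the usual large-sample interval. Wilson's interval gives nearly the same half-widths (11.0 points at 40, 9.9 at 50). With an exact interval they would be 12.1 points at 40 and 10.7 at 50, so the statement that 50 suffices holds for the former methods only.

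The point calls for a moderate correction of the sample-size text. It does not threaten the trial's validity, and it does not by itself require more enrolment provided day-3 results are nearly complete.

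**What to change.** Correct section 8.1 in one of two ways:

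- state a minimum of 49 patients evaluable at day 3, and note that the target of 50 meets this only if at most one patient lacks a day-3 result; or
- keep 40 and restate the precision as about ±11 points at 95% confidence.

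In either case, name the formula used, and say that the 20% allowance for 28-day losses relates to the day-28 outcomes and not to the day-3 endpoint.

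The cost is a rewording of one section. The second option also means a slightly less favourable stated precision. Enrolment would need to rise only if the sponsor chose the first option and expected more than one missing day-3 result.

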8.2 Analysis of data

WHO excel programme and SPSS programme will be used for data management and analysis. Data will be analysed by two methods: the Kaplan-Meier method and per-protocol analysis. In addition to the reasons for withdrawal listed in section 3.8, patients will be considered withdrawn from the analysis if the PCR results are unclassifiable or if the results of PCR indicate that the failure is due to reinfection with *P. falciparum* or *P. vivax.*

The final analysis will include:

- a description of all patients screened and the distribution of reasons for non-inclusion in the study;
- a description of all the patients included in the study;
- the number of adverse events and serious adverse events in all the patients included in the study;
- the proportion of patients lost to follow-up or withdrawn, with 95% confidence intervals and a list of reasons for withdrawal;
- the cumulative incidence of success and failure rates at day 28, PCR-uncorrected and PCR-corrected; and
- the proportion of early treatment failure, late clinical failure, late parasitological failure and adequate clinical and parasitological response at day 28, with 95% confidence intervals, PCR-uncorrected and PCR-corrected.
- The PCT, parasite reduction rate (slope of the log-linear parasite clearance curve), the parasite reduction rate at 48 hours, and the number of patients parasite positive at day 3;
- The pharmacokinetic profile of the patients.

Guidelines on calculating the cumulative success or failure rate, the proportion of adequate clinical and parasitological response and treatment failure are given in Appendix 9.

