Appendix 4. Classification of treatment outcomes[[5]](#footnote-6)

**Early treatment failure**

- danger signs or severe malaria on day 1, 2 or 3 in the presence of parasitaemia;
- parasitaemia on day 2 higher than on day 0, irrespective of axillary temperature;
- parasitaemia on day 3 with axillary temperature ≥ 37.5 ºC;
- parasitaemia on day 3 ≥ 25% of count on day 0.

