Appendix 9. Guidelines for analysis of results

| **End-point for day X**  **(X = 28)** | **PCR-uncorrected results** | |
| --- | --- | --- |
| **Cumulative success or failure rate (Kaplan-Meier analysis)** | **Proportion**  **(per-protocol analysis)** |
| Adequate clinical and parasitological response on day X | Success | Success |
| Early treatment failure | Failure | Failure |
| Late clinical failure before day 7 | Failure | Failure |
| Late clinical failure or late parasitological failure on or after day 7 | Failure | Failure |
| Other species infection | Censored day of infection | Excluded from analysis |
| Lost to follow-up | Censored last day of follow-up according to timetable | Excluded from analysis |
| Withdrawal and protocol violation | Censored last day of follow-up according to timetable before withdrawal or protocol violation | Excluded from analysis |

| **End-point for day X**  **(X = 28)** | **PCR-corrected results** | |
| --- | --- | --- |
| **Cumulative success or failure rate (Kaplan-Meier analysis)** | **Proportion**  **(per-protocol analysis)** |
| Adequate clinical and parasitological response at day X | Success | Success |
| Early treatment failure | Failure | Failure |
| Late clinical failure before day 7 | Failure | Failure |
| Late clinical failure or late parasitological failure on or after day 7 |  |  |
| - falciparum recrudescence* | Failure | Failure |
| - falciparum reinfection* | Censored day of reinfection | Excluded from analysis |
| - other species mixed with falciparum recrudescence | Failure | Failure |
| - other species mixed with falciparum reinfection | Censored day of reinfection | Excluded from analysis |
| - other species infection | Censored day of infection | Excluded from analysis |
| - undetermined or missing PCR | Excluded from analysis | Excluded from analysis |
| Lost to follow-up | Censored last day of follow-up according to timetable | Excluded from analysis |
| Withdrawal and protocol violation | Censored last day of follow-up according to timetable before protocol violation or withdrawal | Excluded from analysis |

* WHO. *Methods and techniques for clinical trials on antimalarial drug efficacy: genotyping to identify parasite populations*.
Geneva, World Health Organization, 2008 (<http://www.who.int/malaria/resistance>).

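### Early treatment failure is settled by day 3 but reported on the day-28 per-protocol denominator, which biases its proportion modestly upward

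*Protocol*

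**What the plan says.** - Protocol, section 8.2, lists "the proportion of early treatment failure, late clinical failure, late parasitological failure and adequate clinical and parasitological response at day 28", with 95% confidence intervals, both PCR-uncorrected and PCR-corrected. It adds: "Guidelines on calculating the cumulative success or failure rate, the proportion of adequate clinical and parasitological response and treatment failure are given in Appendix 9".
- Appendix 9, in both the PCR-uncorrected and the PCR-corrected table, has the row "Early treatment failure | Failure | Failure". The first entry is for Kaplan-Meier, the second for the per-protocol proportion.
- Appendix 9 treats loss differently in the two columns: "Lost to follow-up | Censored last day of follow-up according to timetable | Excluded from analysis". In the per-protocol column, withdrawals, protocol violations and other-species infections are also excluded. The PCR-corrected table further excludes falciparum reinfections and undetermined or missing PCR results.
- Appendix 4 decides ETF on days 1 to 3. The latest criteria refer to day 3, for example "parasitaemia on day 3 with axillary temperature ≥ 37.5 ºC". Section 3.3 keeps patients in hospital for the first 7 days.
- Section 8.1 sets the allowance: "With a 20% increase to allow loss to follow-up and withdrawals during the 28-day follow-up period". The target is 50 patients.

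**The concern.** A proportion should be taken over the patients in whom the event could have been observed. For ETF these are the patients whose status is known at day 3. Appendix 9 instead uses those who still have a valid classification at day 28.

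A patient who is lost on day 14, for instance, has already been observed not to be an ETF, yet is removed. A patient who was an ETF has reached an end-point. Section 5.1.1 does not require later results for that patient to be recorded systematically, so later loss does not remove him or her. Membership of the denominator therefore depends on the outcome being counted.

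The proportion with ETF is one of the specific objectives in section 2, and the results are to be compared with data from Cambodia and Thailand. An ETF percentage that grows with later dropout makes such a comparison partly a comparison of follow-up rates.

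**Working it through.** **Inputs**
- Target of 50 patients and 20% allowance: section 8.1. The step from 40 to 50 reproduces as 40 / (1 − 0.20) = 50, so the allowance is 10 of 50 patients. (The minimum of 40 does not follow from its own inputs: 1.96² × 0.15 × 0.85 / 0.10² = 48.98, so 49. That is a separate matter and is not relied on here.)
- Expected ETF rate: not stated in the protocol. Assumed range 2% to 10%, that is 1 to 5 of 50.
- Assumed: all 50 have a known day-3 classification and all exclusions come after day 3.

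**Step 1: direction.** Let E be the number of ETFs, N the number with known day-3 status, and k the number of non-ETFs excluded after day 3. The proportion sought is E/N; the reported one is E/(N − k). The ratio is N/(N − k), which exceeds 1 whenever k > 0, whatever the reason for exclusion. With N = 50:
- k = 2: 50/48 = 1.04
- k = 5: 50/45 = 1.11
- k = 10: 50/40 = 1.25
- k = 15 (assumed, beyond the allowance): 50/35 = 1.43

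**Step 2: size if 20% of non-ETFs are excluded.** Reported proportion = E / (E + 0.8 × (50 − E)).

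| E | True | Calculation | Reported |
|---|---|---|---|
| 1 | 2% | 1/40.2 | 2.5% |
| 2 | 4% | 2/40.4 | 5.0% |
| 3 | 6% | 3/40.6 | 7.4% |
| 5 | 10% | 5/41.0 | 12.2% |

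**Step 3: size against imprecision.** Removing exactly 10 of 50, with Clopper-Pearson 95% intervals:

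| E | Over 50 | Over 40 |
|---|---|---|
| 1 | 2.0% (0.1 to 10.6) | 2.5% (0.1 to 13.2) |
| 2 | 4.0% (0.5 to 13.7) | 5.0% (0.6 to 16.9) |
| 3 | 6.0% (1.3 to 16.5) | 7.5% (1.6 to 20.4) |
| 5 | 10.0% (3.3 to 21.8) | 12.5% (4.2 to 26.8) |

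The shift is 0.5 to 2.5 points, well inside each interval.

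**Step 4: the PCR split.** Under section 5.2.5, follow-up samples for genotyping are taken on and after day 7, and Appendix 9 treats ETF identically in both tables. PCR therefore cannot change an ETF. Reinfections count as failures, and stay in the denominator, when uncorrected; they leave it when corrected. Illustration with assumed counts: 3 ETFs among 40 is 7.5%; if 4 of the 40 are reinfections, the corrected figure is 3/36 = 8.3%. The same three patients produce two rates.

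**The case against.** **The per-protocol percentages are a coherent set.** Sections 3.7 and 3.8 assign no outcome to lost or withdrawn patients, and the four categories are shares of the patients classified at day 28 that sum to 100%. This is true as description. But section 2 uses the ETF proportion as an indicator of efficacy, and a share that moves with later loss or with PCR results is a poor one.

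**The size is easily overstated.** This stands. The 20% covers all losses and withdrawals over 28 days, including those before day-3 status is known (vomiting twice, missed visits in the first 3 days), who are rightly left out. It is thus an upper case for that allowance. The assumed ETF range may also be high: the nearest figure in the background section is one ETF among 168 + 153 = 321 completed patients, about 0.3%, on combination treatments.

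**Not every early failure is kept.** This also stands. Enrolment violations (section 3.8) and inconclusive thin films (section 5.2.4) are excluded even if the patient was an ETF. The point concerns valid ETFs.

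**Stronger readings a reader might infer**
- *That total day-28 failure is overstated.* This needs an assumption that the documents cannot supply. If loss is non-informative, a true 10% (4% early, 6% late) with 20% loss in equal steps before days 14, 21 and 28 would appear as about 11.3% per protocol. If patients who would have failed are more often lost, the error could reverse.
- *That the protocol must name a headline method.* Section 8.2 states: "Data will be analysed by two methods: the Kaplan-Meier method and per-protocol analysis". Both will be reported, with losses and reasons, so any gap is visible, and the choice can be left to an analysis plan.
- *That the resistance conclusion is compromised.* The background section calls day-3 positivity the best measure of slow clearance, and section 8.1 sizes the study on it. Section 8.2 lists it separately as a number. Neither it nor parasite clearance time uses this denominator.

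**Conclusion.** The point holds for the ETF proportion. Its upward bias follows from the arithmetic and needs no assumption about why patients are lost. It is zero if there are no ETFs or nobody is excluded after day 3. At the upper case of the protocol's allowance, the relative overstatement is about a quarter: 0.5 to 2.5 points for an assumed true ETF of 2% to 10%, small beside the confidence interval.

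The Kaplan-Meier day-28 failure estimate does not share the mechanism for loss, withdrawal, other-species infection or reinfection, because those patients are censored and so remain at risk on day 3. One qualification: Appendix 9 removes undetermined or missing PCR results from the corrected Kaplan-Meier analysis as well.

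This is not a gap that an analysis plan would be expected to fill, because Appendix 9 already fixes the exclusion rule.

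**What to change.** In section 8.2 and Appendix 9, report the ETF proportion with its 95% CI over all eligible patients with a known day-3 classification, regardless of later loss or exclusion. Give it as a single figure, not split by PCR correction. Keep the day-28 per-protocol set for late clinical failure, late parasitological failure and adequate clinical and parasitological response.

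The change is to analysis wording only and needs no new data, since the day-3 assessments are already scheduled. The cost is that the four category percentages no longer share one denominator or sum to 100%, so each needs its own denominator printed beside it.
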